### Baseline Data

Information on participant demographics (age, gender, type of health insurance, and smoking and drinking history), stroke history (stroke onset and initial diagnosis date; the type and date of computed tomography or magnetic resonance imaging used to diagnose the stroke; the site, type and lesion of the stroke; the Trial of Org 10172 in acute stroke treatment classification for cerebral infarction; history of stroke surgery; stroke risk factors; and past medical history), stroke symptoms (hemiplegia, sensory disorder, dysphagia, dysuria, dyspnea, digestive disorder, poststroke depression, poststroke delirium, poststroke insomnia, poststroke cognitive impairment, headache, dizziness, fatigue, and other symptoms), laboratory findings (complete blood count, biochemistry, lipid profile, and endocrine panel), and stroke assessment (hemiplegia with the manual muscle testing grading system, modified Ashworth scale, and grasp power; gait and balance disorders with the WIN-TRACK and timed up and go test; activities of daily living with the modified Barthel index; fatigue with the fatigue assessment scale and fatigue severity scale; stroke scales with the National Institutes of Stroke scale, Korean standard pattern identification for stroke questionnaire, and heart-kidney noninteraction questionnaire; impaired memory and disorientation with the Korean version of the mini-mental state examination; and depression with the patient health questionnaire-9) will be collected from medical records at the time of the first outpatient visit or inpatient admission. Detailed information regarding the collection of each item is presented in Table 1, and the participant timeline is presented in Table 2.

**Table 1 table1:** Collecting information from participants.

Item	Information collected
Demographics	Age, gender, type of health insurance (national health insurance, medical benefits, or other), smoking history (status, past and present smoking, and amount of smoking), drinking history (status, past and present drinking, amount of drinking by type, and duration of drinking).
Stroke history	Stroke onset date and initial diagnosis date, the type and date of the imaging test used to diagnose the stroke (CT^a^ or MRI^b^), the site of the stroke (cortical area or subcortical area), the type of stroke (cerebral infraction, cerebral hemorrhage, or subarachnoid hemorrhage), the lesion of the stroke (ACI^c^, LACI^d^, or POCI^e^), TOAST^f^ classification for cerebral infarction (LAA^g^, CE^h^, SVO^i^, other causes, or undetermined), history of stroke surgery, stroke risk factors (previous stroke, hypertension, dyslipidemia, diabetes mellitus, atrial fibrillation, or others), and past medical history (date of diagnosis or surgery, name of disease or surgery, and current status).
Stroke symptoms	Hemiplegia (motor disorder), sensory disorder (including central pain), dysphagia (applying L-tube, PEG^j^, or dysphagia diet), dysuria (applying foley catheter), dyspnea (applying tracheostomy tube or oxygen), digestive disorder (constipation, dyspepsia, diarrhea, or others), poststroke depression (taking antidepressant or suspected depression on a depression-related scale), poststroke delirium, poststroke insomnia, poststroke cognitive impairment (taking drugs related to cognitive impairment or suspected cognitive impairment on a scale such as MMSE-K^k^), headache, dizziness, fatigue, and other symptoms.
Laboratory findings	Complete blood count (white blood cell; red blood cell; hemoglobin; hematocrit; platelet; differential count, including segmented neutrophils, lymphocytes, monocytes, eosinophils, and basophils; PT-INR^l^; and aPTT^m^), biochemistry (total bilirubin, protein, albumin, AST^n^, ALT^o^, BUN^p^, creatinine, sodium, potassium, chloride, calcium, uric acid, and glucose) , lipid profile (total cholesterol, triglyceride, HDL^q^-cholesterol and LDL^r^-cholesterol), and endocrine panel (hemoglobin A1C).
Stroke assessments	Hemiplegia with the MMT^a^, MAS^t^, and grasp power; gait and balance disorders with WIN-TRACK^u^ and TUG^u^ test; ADL^v^ with MBI^w^ and fatigue with FAS^x^ and FSS^y^; stroke scale with the NIHSS^z^, K-SPI^aa^ stroke questionnaire, and heart-kidney noninteraction questionnaire; impaired memory and disorientation with the MMSE-K; and depression with the PHQ-9^ab^
Korean medicine treatments	Herbal medicine (prescription name, administration purpose and duration, current administration, frequency, single dose, and unit), acupuncture (method, frequency, and duration), electroacupuncture (stimulus method, frequency, and duration), bee venom acupuncture (type and method, frequency, and duration), pharmacopuncture (type and method, frequency, and duration), indirect moxibustion (method, frequency, and duration), direct moxibustion (method, frequency, and duration), and cupping (method, frequency, and duration)
Rehabilitation therapies	Physical therapy, occupational therapy, speech therapy, and swallowing therapy
Concomitant treatment	Western medicine (ingredient name, administration purpose and duration, current administration, frequency, single dose, unit, route of administration)
Safety outcomes	Spot bleeding (bleeding time <10 s), microbleeding 1 (bleeding time 10 s to <20 s), microbleeding 2 (bleeding time 20 s to <30 s), extensive bleeding (bleeding time ≥30 s), massive hemorrhage influencing vital signs or causing other complications, bruising (checked 1-3 hours after removing the needles), edema, faintness or dizziness, fatigue or exhaustion, nausea or vomiting, pneumonia, needle fracture, skin eruption or itching, pain after needling, and other adverse effects after each treatment

^a^CT: computed tomography.

^b^MRI: magnetic resonance imaging.

^c^ACI: anterior circulation infarct.

^d^LACI: lacunar infarct.

^e^POCI: posterior circulation infarct.

^f^TOAST: Trial of Org 10172 in Acute Stroke Treatment.

^g^LAA: large-artery atherosclerosis.

^h^CE: cardioembolism.

^i^SVO: small vessel occlusion.

^j^PEG: percutaneous endoscopic gastrostomy.

^k^MMSE-K: Mini-mental state examination, Korean version.

^l^PT-INR: prothrombin time-international normalized ratio.

^m^aPTT: activated partial thromboplastin time.

^n^AST: aspartate aminotransferase.

^o^ALT: alanine aminotransferase.

^p^BUN: blood urea nitrogen.

^q^HDL: high-density lipoprotein.

^r^LDL: low-density lipoprotein.

^s^MTT: manual muscle testing grading system.

^t^MAS: modified Ashworth scale.

^u^TUG: timed up and go.

^v^ADL: activities of daily living.

^w^MBI: modified Barthel index.

^x^FAS: fatigue assessment scale.

^y^FSS: fatigue severity scale.

^z^NIHSS: National Institutes of Stroke scale.

^aa^K-SPI: Korean standard pattern identification.

^ab^PHQ-9: patient health questionnaire-9.

**Table 2 table2:** Participant timeline for the Registry of Stroke in Korean Medicine Hospital.

Item	Outpatient first visit or inpatient admission day	At each outpatient visit or every day during hospitalization	Every 4 weeks after the outpatient first visit or inpatient admission day	Immediately after each acupuncture or pharmacopuncture. therapy	Final outpatient visit or upon discharge
Demographics	●				
Stroke history	●				
Stroke symptoms	●				
Laboratory findings	●				●
Stroke assessments^a^	●		●		
Stroke assessments^b^	●				
Korean medicine treatments		●			
Rehabilitation therapies		●			
Concomitant treatment		●			
Safety outcomes				●	

^a^Hemiplegia with the manual muscle testing grading system, modified Ashworth scale, and grasp power; gait and balance disorders with WIN-TRACK and the timed up and go test; activities of daily living with the modified Barthel index; fatigue with the fatigue assessment scale and fatigue severity scale; stroke scale with the National Institutes of Stroke scale, Korean standard pattern identification-stroke questionnaire, and heart-kidney noninteraction questionnaire; impaired memory and disorientation with the mini-mental state examination, Korean version; and depression with the patient health questionnaire-9.

^b^Impaired memory and disorientation with the mini-mental state examination, Korean version, and depression with the patient health questionnaire-9.

### Korean Medicine Treatments

Information on the use of herbal medicines (including herbal decoctions, inpatient pharmaceuticals, and external pharmaceuticals), acupuncture, electroacupuncture, bee venom acupuncture, pharmacopuncture, indirect moxibustion, direct moxibustion, and cupping during outpatient visits and hospitalizations will be collected daily (ie, at each outpatient visit or daily during hospitalization). The start and end dates of each treatment tool will also be investigated. If the use of any treatment tool has been discontinued, the date on which it was discontinued shall be the primary end date, the date the treatment was resumed shall be the secondary start date, and the date the treatment was last used shall be the secondary end date. For herbal medicine and pharmacopuncture, the prescription name will be written separately in the comments section of the eCRF. For herbal medicines, the start and end dates of each prescription will be recorded whenever the prescription is changed.

### Rehabilitation Therapies

Information on the use of physical, occupational, speech, and swallowing therapies during outpatient visits and hospitalizations will be collected every day (ie, at each outpatient visit or daily during hospitalization). The duration of each treatment will be recorded in the same way as that for the KM treatment.

### Concomitant Treatment

We will also collect information on the daily use of western medications (oral and injection types) every day (ie, at each outpatient visit or daily during hospitalization). For each western medicine, the name of the ingredient, purpose of administration, start date, end date, frequency of administration, dose, unit, and route will be investigated. If the frequency, dose, unit, and route change for the same ingredient, information will be collected separately.

### Follow-Up Measures

Stroke assessments (outlined in Table 2) will be conducted every 4 weeks after the first visit for both outpatients and inpatients. Follow-up laboratory findings will be collected at the final outpatient visit or discharge.

### Safety Outcomes

During the treatment period, the safety of acupuncture treatments will be evaluated when the needles are removed immediately after each acupuncture, electroacupuncture, pharmacopuncture, or bee venom acupuncture treatment. Bleeding events with duration and complications, bruising, edema, faintness or dizziness, fatigue or exhaustion, nausea or vomiting, pneumonia, needle fracture, skin eruption or itching, pain after needling, or other adverse events after each treatment will be assessed. The detailed safety assessment items are listed in Table 1.

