**Objective:**

We aimed to collect and analyze data on the major clinical characteristics of patients with stroke receiving KM treatment and investigate the effectiveness and safety of KM in the Korean population.

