**Methods:**

The Registry of Stroke in Korean Medicine Hospital (RoS-KoMH) is a prospective, multicenter, observational disease registry aimed at collecting data from 500 sets of patients at multiple timepoints. Eligible adult patients diagnosed with cerebral infarction, cerebral hemorrhage, or subarachnoid hemorrhage who visited 4 KM hospitals as outpatients or inpatients will be continuously registered using the electronic case report form. Baseline data at the first visit; KM treatment, rehabilitation therapy, and concomitant therapy during the visit; stroke evaluation every 4 weeks after the first visit; laboratory findings at discharge or the last visit; and safety evaluation information after each acupuncture or pharmacopuncture treatment will be collected.

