### Data Analysis

Statistical analyses will be performed with SPSS version 21.0 (IBM Corporation) by our biostatisticians at the RoS-KoMH. Descriptive statistics will be used to analyze the data, and all measures will be presented as means (SDs) for continuous variables and n (%) for dichotomous variables. For variables assessed more than once, the amount or rate of change from baseline to follow-up will be calculated.

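### The registry's safety aim covers all Korean medicine, but adverse events are scheduled for recording only around needling sessions, and the timing of the bruising check is inconsistent

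*Protocol article*

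**What the plan says.** All references are to the protocol article.

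- **Aim.** The abstract's Objective is to "investigate the effectiveness and safety of KM in the Korean population". The Introduction and the limitations paragraph of the Discussion also speak of safety for KM treatment generally, without limiting it to needling.
- **Exposure.** Table 1 and the Korean Medicine Treatments section list eight modalities. Use of the non-needling ones is recorded as closely as the rest: "indirect moxibustion, direct moxibustion, and cupping during outpatient visits and hospitalizations will be collected daily", and herbal medicine falls under the same rule.
- **Adverse events, text.** Under Safety Outcomes, "the safety of acupuncture treatments will be evaluated when the needles are removed immediately after each acupuncture, electroacupuncture, pharmacopuncture, or bee venom acupuncture treatment".
- **Adverse events, schedule.** In Table 2 the safety row has a single mark, in the column headed "Immediately after each acupuncture or pharmacopuncture. therapy". The abstract's Methods say "safety evaluation information after each acupuncture or pharmacopuncture treatment will be collected".
- **Bruising.** The safety row of Table 1 has "bruising (checked 1-3 hours after removing the needles").
- **Laboratory tests.** Table 2 and Follow-Up Measures place these at the first visit or admission and at the final visit or discharge. They include liver enzymes, blood urea nitrogen and creatinine, but they are listed as laboratory findings, not as safety outcomes.

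**The concern.** A safety conclusion can reach only as far as the events that were looked for. Here exposure to every modality is documented daily or at each visit, while the recording of harms is triggered by needling alone. If the report then speaks of the safety of KM, readers will apply it to herbal medicine, moxibustion and cupping, for which no adverse event record was scheduled. The Discussion makes this more pointed. It cites earlier work on herbal medicine combined with warfarin, and on liver and kidney function under combined herbal and western medicine, and then notes that the quality of the evidence has been criticised.

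Timing raises a second issue. Some listed events, such as pneumonia or skin eruption, may not be apparent when a needle comes out, and no later enquiry is scheduled. Bruising is the one item with a later check, but that check does not fit the schedule in the text and Table 2. Sites could therefore follow different rules for the same variable.

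**Working it through.** No event rate, power or precision figure is stated, so there is no figure of the plan to reproduce. The check is a comparison of the sections, with two simple counts.

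**Step 1. Modalities against adverse event triggers.** Modalities come from Table 1 and Korean Medicine Treatments; triggers come from Safety Outcomes.

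| Modality | Use recorded daily or per visit | Adverse event recording scheduled |
|---|---|---|
| Acupuncture | yes | yes |
| Electroacupuncture | yes | yes |
| Pharmacopuncture | yes | yes |
| Bee venom acupuncture | yes | yes |
| Herbal medicine | yes | no |
| Indirect moxibustion | yes | no |
| Direct moxibustion | yes | no |
| Cupping | yes | no |

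Without a trigger: 8 − 4 = 4 of 8 modalities.

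**Step 2. Is another safety record scheduled elsewhere?** In Table 2 the safety row is blank under the first visit, the daily or per-visit column, the 4-weekly column and the final visit. Safety Outcomes, Table 2 and the abstract agree on this, so it is not a slip in one place.

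**Step 3. What partial coverage exists?**
- Laboratory tests at the start and end could show some hepatic or renal effect of herbal medicine. They do not record clinical events and are not tied to a modality.
- The safety list ends with an open category for other adverse events after each treatment. In Safety Outcomes and Table 2 the sessions that trigger the list are needling sessions. A patient needled repeatedly might mention an earlier or non-needling event, but nothing asks for it and no suspected modality is listed for recording.
- The fatigue scales are repeated every 4 weeks, but they do not attribute a change to a treatment.

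**Step 4. Bruising time.**

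| Place | Time of assessment |
|---|---|
| Safety Outcomes | at needle removal |
| Table 2, column heading | immediately after treatment |
| Table 1, safety row | 1-3 hours after needle removal |

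The first two agree and the third does not. The article does not say how the later check is made for outpatients.

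**Step 5. How much collection remains?** Number of Participants gives a target of 500 sets. Results gives 410 sets by September 25, 2024.
- Collected: 410 / 500 = 82%.
- Remaining: 500 − 410 = 90 sets, 90 / 500 = 18%.

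A set is not a patient: one patient with assessments at two follow-up times gives two sets. The abstract calls the same 410 participants. The set count is used here because the target is stated in sets. Recruitment is scheduled to end on December 31, 2026, so fewer than 90 sets may remain when a change takes effect.

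**The case against.** The strongest reply has four parts.

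1. **The bruising times need not conflict.** Safety Outcomes refers the reader to Table 1 for detail, and Table 1 gives one item its own later time. That can be read as a specific rule refining a general one. This is fair, and it makes the bruising point a mismatch to reconcile, not a proven error in what sites do. It does not remove the mismatch, because Table 2 schedules the whole safety row at a single immediate time.

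2. **Non-needling harms are not wholly unseen.** A reader might infer that such harms will appear as zero and that the registry will declare KM safe. The documents do not support this. The open item at repeated sessions and the laboratory tests give some coverage, no analysis had been done at the time of writing, and the stated purpose is exploratory. What stands is that this coverage is incidental, so an absence of recorded events could not be read as an absence of harm.

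3. **Differential bruising rates are conjecture.** A reader might also infer that inpatient and outpatient rates will differ through ascertainment alone. The article does not say how long outpatients stay or how they are checked, so this is a possibility only.

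4. **Analysis detail belongs elsewhere.** How laboratory abnormalities are tabulated, or how repeated sessions per patient enter an interval estimate, is commonly left to a statistical analysis plan, and none is shown. These are not part of this point. The collection schedule is different: the article states it outright, and no analysis can recover events that were not recorded.

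The reply is also right that a form change would be late and not trivial. The electronic case report form took about 10 months to develop across the four institutions, and four review boards approved the protocol.

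**Conclusion.** The point holds as a mismatch between the safety aim and the safety data. Four of eight modalities have no scheduled adverse event recording, and no look-back for delayed events is specified for any modality. The single timed exception is the bruising check, which itself does not match the immediate assessment in the text and Table 2. As scheduled, the data can support a description of adverse events observed around needling sessions, plus laboratory change between first and last visit. They cannot support a conclusion on the safety of KM as a whole.

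The size of any missed harm cannot be given, because the documents contain no event rates. The conclusion assumes that the schedule in the article is the one in use. Three concordant statements of it make that reasonable. It also assumes that no separate adverse event reporting route exists outside the article; if one does, it should be cited and the point narrowed accordingly.

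**What to change.** 1. **Main change, wording only.** Restrict the safety objective and conclusions to adverse events observed around needling sessions, and report laboratory change separately. State that adverse events of herbal medicine, moxibustion and cupping were not systematically recorded. The cost is a narrower claim.

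2. **If the sponsor wants to keep the broader aim.** Add one item to the existing daily or per-visit record: any adverse event since last contact, with the suspected modality. Report it only for patients in whom it was collected. The cost is some extra data entry, an amendment to the case report form with review board approval, and no such data for the roughly 410 sets already collected. At most about 18% of the target (90 sets) could benefit, counted at September 25, 2024.

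3. **Bruising.** Reconcile the timing between Safety Outcomes, Table 1 and Table 2, so that one statement says when the check is made and for whom. Use only sessions actually checked as the denominator. This needs a clarification to sites and a record of whether the check was done.

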### Data Analysis

Statistical analyses will be performed with SPSS version 21.0 (IBM Corporation) by our biostatisticians at the RoS-KoMH. Descriptive statistics will be used to analyze the data, and all measures will be presented as means (SDs) for continuous variables and n (%) for dichotomous variables. For variables assessed more than once, the amount or rate of change from baseline to follow-up will be calculated.

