### Number of Participants

The purpose of this study was not to statistically verify the intervention effect of KM treatment for stroke but to explore the demographics, clinical aspects, treatment status, and therapeutic efficacy and safety of KM for patients with stroke patients in Korea and to provide clinical evidence to improve the therapeutic effect of KM treatment in the future.

Accordingly, a total of 500 sets of clinical information on patients with stroke will be collected based on the opinions of the researchers, considering the financial resources, the environment in which the study is conducted, and the appropriate number needed to achieve the goal. One set was defined as a stroke patient for whom information was collected at the time of the first outpatient visit or admission, and additional information was collected at any point (4, 8, or 12 weeks) after the first outpatient visit or admission. For example, if information was collected for a single patient once upon admission, once in the fourth week of hospitalization, and once again in the eighth week of hospitalization, 2 sets of information would be considered collected.

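### Mean (SD) and change from baseline, the default for all continuous measures, would not show how many patients moved from normal to clearly abnormal liver or kidney values

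*Protocol article*

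**What the plan says.** All references are to the protocol article.

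- **Default summary (Data Analysis).** "all measures will be presented as means (SDs) for continuous variables and n (%) for dichotomous variables". The next sentence adds: "For variables assessed more than once, the amount or rate of change from baseline to follow-up will be calculated".
- **Laboratory values (Table 1, under Baseline Data).** The list includes "biochemistry (total bilirubin, protein, albumin, AST^n^, ALT^o^, BUN^p^, creatinine" and further analytes. No reference range, threshold, grade or abnormal flag is given for any of them.
- **Timing (Follow-Up Measures; Table 2).** Laboratory values are taken at the first visit or admission, and then: "Follow-up laboratory findings will be collected at the final outpatient visit or discharge". Each patient therefore has at most one scheduled follow-up value per analyte.
- **Treatments recorded (Table 1).** The first Korean medicine (KM) treatment listed is "Herbal medicine (prescription name, administration purpose and duration, current administration, frequency, single dose, and unit".
- **Safety Outcomes.** The section states that "the safety of acupuncture treatments will be evaluated when the needles are removed immediately after each acupuncture" or a related needle treatment. The listed items are bleeding, bruising, pain after needling and similar events, plus other adverse events after each treatment. No laboratory abnormality is listed.
- **Aims.** The Objective in the Abstract is to "investigate the effectiveness and safety of KM in the Korean population". Number of Participants describes the purpose as to "explore the demographics, clinical aspects, treatment status, and therapeutic efficacy and safety of KM for patients with stroke patients in Korea".

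**The concern.** Safety of KM is an aim, and herbal medicine is part of KM. The scheduled safety assessment is tied to needle removal, so it is not designed to pick up a liver or kidney effect of an oral prescription. The baseline and final AST, ALT, bilirubin, creatinine and BUN are the main scheduled data that can.

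For such values, a safety description needs the number of patients who started normal and ended clearly abnormal. A mean and an SD describe the group and do not determine that number. Amount of change is again a group average, and rate of change most naturally means relative change, not the share of patients who changed category. The n (%) clause could carry the count, but the article defines no yes/no laboratory variable for it to act on.

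If the default were all that was reported, a reader could not tell whether no patient or several patients had a marked rise.

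**Working it through.** The plan has no figure of its own to reproduce: it states no laboratory values, SDs, event rates, alpha or power. The check has two parts.

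**1. Does the default cover these values?** Data Analysis applies mean (SD) to every continuous measure and change from baseline to every repeated one. The five analytes are numeric (Table 1) and are scheduled at baseline and at the final visit or discharge (Table 2, Follow-Up Measures). Both sentences therefore apply, although neither names laboratory values.

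**2. How far does one mean and SD leave the count open?**

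*From the document:* 500 sets. Number of Participants counts one set per follow-up point (4, 8 or 12 weeks), so at 1 to 3 sets per patient there are 500/3 = 167 to 500/1 = 500 patients. The number with both laboratory values could be lower.

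*Assumed, for illustration only:* ALT; 2% of patients affected (3 to 10 patients); each affected patient rises by D = 175 U/L (25 to 200); the others change by 0 on average with SD 15. The main case is N = 300 with k = 6.

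Mean change: M = kD/N = 6 × 175/300 = 3.5.

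Total sum of squares about the mean:
(N−k−1) × 15² + (N−k) × M² + k(D−M)²
= 293 × 225 + 294 × 3.5² + 6 × 171.5²
= 65,925 + 3,601.5 + 176,473.5 = 246,000.

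SD: S = √(246,000/299) = 28.7. The t-based 95% CI for the mean is 0.2 to 6.8.

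Next, hold M and S fixed and ask which other counts j of patients rising by 175 could have produced them. The remaining N−j patients must have

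- mean r = (N·M − 175j)/(N−j), and
- sum of squares Q = (N−1)S² − (N−j)(r−M)² − j(175−M)², which must be at least 0.

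| j | mean change of the others | SD of the others |
|---|---|---|
| 0 | 3.5 | 28.7 |
| 3 | 1.8 | 23.0 |
| 6 | 0.0 | 15.0 |
| 7 | −0.6 | 11.0 |
| 8 | −1.2 | 3.8 |
| 9 | impossible: Q = −26,897 | – |

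So the printed pair 3.5 (SD 28.7) fits 0 to 8 such patients. The j = 0 case need not conceal large rises: if all changes were Normal(3.5, 28.7), the expected number above 95 U/L would be 300 × P(change > 95) = 0.2.

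Other sizes under the same assumptions:

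| N | true k | mean (SD) | 95% CI | counts that fit |
|---|---|---|---|---|
| 167 | 3 | 3.1 (27.6) | −1.1 to 7.4 | 0 to 4 |
| 300 | 6 | 3.5 (28.7) | 0.2 to 6.8 | 0 to 8 |
| 500 | 10 | 3.5 (28.7) | 1.0 to 6.0 | 0 to 13 |

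Sensitivity at N = 300 with 6 true cases, showing the largest fitting count (the smallest is 0 throughout):

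| rise (U/L) | others' SD 10 | SD 15 | SD 25 |
|---|---|---|---|
| 100 | 8 | 12 | 23 |
| 175 | 6 | 8 | 11 |
| 275 | 6 | 6 | 8 |

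The width of the range depends on the assumptions. In every setting, none and all six of the true cases are both compatible with the printed summary.

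**The case against.** The strongest reply is that this is a missing detail, not a mistake. The source is a condensed journal article, its analysis plan is not shown, and shift tables and thresholds normally live there. Data Analysis is a short default, and its n (%) clause is the very format a derived flag would use. This largely stands. A reader might infer that the protocol rules out counting abnormal values; it does not, and a later plan could add the count without contradiction. What remains is that the article does not simply stay silent: it names one summary for all measures, and that summary alone cannot give the count.

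Second, the safety role of these values is an inference. Table 1 lists laboratory findings apart from safety outcomes. A reader might take the values to be designated safety endpoints, but the article never says so. Liver and kidney safety appears in the Discussion only as earlier published work. The link runs through the general safety aim and the needle-bound safety schedule.

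Third, the magnitude is wholly assumed, and the planned summary would not be blind. In the main case the SD of change goes from 15 to 28.7 and the CI excludes 0, so a careful reader might suspect outliers. The claim that mean (SD) would hide the problem altogether is therefore too strong: it may hint at outliers but cannot count them. The counts also refer to rises of exactly 175 U/L, and the upper end of 8 needs the other 292 patients to have an SD of only 3.8.

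Fourth, a count would not settle whether herbal medicine is safe. There is one follow-up value, western medicines run alongside, and the Discussion itself says causal inference may be limited. That stands in full.

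**Conclusion.** The point holds as a modest reporting improvement. Taken literally, the default would describe AST, ALT, total bilirubin, creatinine and BUN without showing how many patients went from normal to clearly abnormal. That count is the more useful description for the herbal medicine part of the safety aim.

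That a mean and SD do not determine a count needs no assumption. The size of the ambiguity (0 to 8 at N = 300; upper limits of 6 to 23 across the sensitivity settings) rests entirely on assumed ALT values and is illustrative. No sample size, test or error rate is affected, and the individual values remain available. The priority is optional to modest.

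**What to change.** Keep mean (SD) and change from baseline. Add one or two sentences to Data Analysis, fixed before any analysis is run:

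1. For each of AST, ALT, total bilirubin, creatinine and BUN, present a baseline-by-final shift table graded against each site's upper limit of normal (ULN). For AST and ALT the categories could be at or below ULN, above ULN to below 3 times ULN, and 3 times ULN or more. Cut-offs for bilirubin, creatinine and BUN should also be set in advance.
2. From each table, report n/N (%) of patients who were at or below ULN at baseline and in the top category at the final value. N is the number of patients who were normal at baseline and have both values.

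The grading matters. A plain normal/abnormal shift table gives no degree, and a count of high final values would include patients already high at entry. The report should say that the count describes patients and does not attribute the change to herbal medicine.

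The cost is a few extra tables and collecting the reference ranges of four sites. No new visit, blood test or hypothesis test is needed. The Results section says no data analysis has yet been done, so the cut-offs can still be set in advance.
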